### Phase one

Phase one will use a co-design process with researchers, teachers, and students. Only students in Group 1 will participate in this phase. The co-design will be conducted as part of the HPE curriculum. The Australian curriculum includes content descriptions related to designing fitness plans and modifying systems to allow students to enjoy and succeed [15], which are aligned with the co-design of HIIT workouts.

The development of the HIIT workouts will take place during obligatory HPE lessons. Students will complete approximately 6 lessons focused on problem identification, upskilling, design, and modification in an iterative process as recommended in the Framework by *Leask* et al. [19]. The number of lessons can be adjusted to meet the needs of participating schools but will encompass the topics outlined in Table 1. The pedagogical strategies will also be modifiable based on the needs of schools and teachers. The lessons may occur during different content units depending on the school and teacher. The same researcher will facilitate the lessons during the co-design process in each participating class.

**Table 1 Tab1:** Topics covered in HIIT Co-design

**Problem Identification**	• Students brainstorm their barriers and facilitators to exercise • Students group their barriers and facilitators into main themes visually with sticky notes • Collectively, students, teachers, and researchers, use the barriers and facilitators to create evaluation criteria that can be used to design and evaluate HIIT workouts
**Upskilling**	• In groups, students discuss what they already know about HIIT • Students explore their heart rate using monitors and Polar GoFit software that shows intensity levels in different colours • Students partake in several HIIT workouts, reflect on their heart rate, and rate the workouts using their class criteria
**HIIT Design**	• Collectively decide, with students, teachers, and researchers, the percentage of heart rate maximum to be classified as high-intensity, and the minimum and maximum interval lengths prior to starting the workout design (HIIT parameters) • In groups, students identify potential themes for HIIT workouts and exercises that fit the theme • In groups, students create HIIT workouts that meet both the HIIT parameters and their evaluation criteria
**HIIT Piloting**	• Each group presents their workout to the class with the aid of the teacher and researchers • Students provide feedback on other groups’ HIIT workouts based on their evaluation criteria, and teachers and researchers to provide one or two comments • Heart rate for each pilot is recorded
**HIIT Modification**	• Each group modifies their workouts based on 1) their own reflection of their pilot; 2) feedback from the other students, researchers, and teachers; and 3) the heart rate summary data from their pilot

The co-design team will include the researcher, the teacher, and the students in each class. The aim and purpose of the sessions will be discussed by each co-design team and students and teachers will be able to provide feedback on the activities and pedagogical strategies used. Each member of the co-design team will be encouraged to share their experiences and expertise through activities designed to elicit collaboration. The co-design team will collectively define the parameters for the HIIT workouts (high intensity threshold and interval length) and criteria for an enjoyable HIIT workout. Based upon these parameters, students will co-design HIIT workouts in small groups, and will subsequently have the opportunity to trial their workouts and receive feedback from the co-design team based on the criteria established and heart rate data. To complete phase 1 activities, the student groups will have an opportunity to modify their workouts based on the feedback they receive.

At the end of the phase one, students will reflect on the co-design process through group discussions and individual written feedback to explore their thoughts about educative outcomes from the lessons, lesson aspects that were enjoyable or beneficial and in what way, their intentions to use the workouts in the future, and suggestions for any changes to the process used. Semi-structured interviews will be conducted with teachers to understand their thoughts on how the co-design lessons related to the curriculum and supported educative outcomes, their intentions to use co-design in the future, and their thoughts on student engagement during the co-design lessons.

### Data collected

Throughout phase 1, the following data will be collected to support the reporting of the methods and results of the co-design process: 1) the criteria created by students to evaluate the workouts; 2) students’ evaluations of pre-made HIIT workouts using their criteria; 3) students’ decisions on HIIT parameters (intensity and interval length); 4) draft HIIT workouts; 5) peer feedback using the criteria on the draft HIIT workouts; 6) heart rate data on draft HIIT workouts; and 7) finalised HIIT workouts.

To evaluate the co-design process, both student and teacher feedback will be collected throughout the process. After each lesson, students will have the opportunity to reflect on the activities and pedagogical strategies used and ask questions or provide suggestions and requests for future lessons, either verbally or written anonymously on an index card. At the end of the process, audio recordings of teacher interviews, notes from student discussions, and individual written feedback from students will be collected to examine the feasibility of co-designing HIIT workouts within the HPE curriculum and relevant outcomes.

### Data analysis

Descriptive statistics will be used to report the methods and results of the co-design process at each school. For example, they will be used to summarise student evaluations of the various HIIT workouts, highlight differences between schools in the created criteria, HIIT parameters, and HIIT workouts. To evaluate the co-design process, a thematic analysis will be completed using students’ feedback about the lesson, notes from student group discussions, individual student written feedback, and semi-structured teacher interviews at the end of the term. The thematic analysis will include familiarisation with the dataset, coding during a re-read of the dataset, and theme development [28, 29]. At least two authors will be involved in refining the themes. Participating teachers will be involved in member checking for feedback on the generated themes. Lastly, the themes will be presented beside quotes which exemplify each theme [28].

### Phase two

Phase two will use a quasi-experimental design and follows the SPIRIT checklist (Additional file 1).

### Intervention

The intervention will consist of the HIIT workouts designed by Group 1 in phase one. Decisions about the delivery, including the number of HIIT sessions per week and the types of lessons where HIIT is delivered (e.g., theory and/or practical lesson), will be made with teachers, and informed by the local school context. The aim is to have two workouts per week completed in practical and/or theory lessons for a duration of 8 weeks within a single 10-week term. Each HIIT workout will take approximately 10-minutes to complete and will be led by the HPE teacher of each class. For teachers who were not involved in the co-design process, a meeting will be scheduled to discuss the HIIT workouts and expectations for the intervention. All involved teachers will also receive a booklet with the HIIT workout (intervals, exercises with descriptions and modifications, and necessary equipment) for each week. The intervention will be completed by Groups 1 (Co-Designers) and 2 (HIIT only). Following the HIIT workout, HPE lessons will continue as normal. Group 3 (Control) will complete the first and last HIIT workout in the 8-week intervention to be able to appropriately respond to the questionnaires focused on HIIT but will otherwise continue with normal HPE lessons.

### Pre-intervention and post-intervention measurements

All intervention measures will be collected by research assistants blinded to group allocation. Baseline measurements will include anthropometry, general enjoyment of physical activity, and self-reported physical activity levels (Fig. 1). These measurements will take place the week prior to the intervention and require approximately 15 minutes to complete. Measurements for cardiorespiratory fitness, muscular power, and executive function will be conducted 1 week prior to and 1 week post intervention and require 60 minutes to complete. Questionnaire data relating to motivation, basic psychological needs, enjoyment, positive and negative affect, and self-efficacy will be collected after the first and last HIIT workout for all groups and will be completed in 10 minutes. Data will be collected using the same protocols at both timepoints. These data will be collected in all 3 groups during HPE lessons.

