#### Phase two:

Determine the effect of a HIIT intervention on cardiorespiratory fitness, muscular fitness, and executive function.Determine the effect of the co-design process on students’ enjoyment, self-efficacy, affect, basic psychological needs, and motivation towards the HIIT workouts.Evaluate whether the intervention was implemented as intended through a process evaluation using the framework described by *Durlak and DuPres* [20].

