## Methods/design

### Overview

*Making a HIIT* will be completed in two phases, occurring during two subsequent terms in the same school year for each participating school. In phase one, students will co-design HIIT workouts with teachers and researchers as a part of their HPE curriculum (Fig. 1). The process will be evaluated using student discussions, student written feedback, and teacher interviews.

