#### Enjoyment

Enjoyment of general physical activity will be measured for all groups using physical activity enjoyment scale (PACES) before the intervention [61]. The version used in adolescents and youth includes the prompt “When I am active” and 16 phrases that students rank on a 5-point Likert scale from 1 (Disagree a lot) to 5 (Agree a lot) [62]. The overall score is calculated by summing the 16 responses and dividing by the number of questions, with a higher score demonstrating greater enjoyment. It has been validated for both children and adolescents [63]. Enjoyment of general physical activity will be used as a covariate for understanding enjoyment of HIIT specifically.

Enjoyment of HIIT will be also measured using the PACES questionnaire. The stem of the questionnaire will be changed from “When I am active” to “When I am participating in HIIT”. Enjoyment has previously been shown to mediate the effects of school-based physical activity interventions and will be a key variable to examine in this study [64]. The PACES questionnaire on HIIT will be used as an outcome variable examining differences in groups and time.

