### Data analysis

Data entry will be completed by one researcher with at least 10% checked by a second researcher. All data will be checked prior to analysis using range to assess any outliers or errors in data entry. To describe the population, descriptive statistics will be reported for each school separately. To determine the effect of the HIIT intervention on cardiorespiratory fitness, muscular fitness, and executive function, general linear models will be used to assess changes in the dependent variables with group (HIIT or control), timepoint, and group x time interaction included as independent variables. To determine the effect of involvement in co-design on students’ motivation, enjoyment, self-efficacy, feelings, and basic psychological needs, generalised linear models will be used to assess changes in the dependent variable, with group (Co-Design or not), timepoint, and group x time interaction included as dependent variables. Potential covariates, such as sex, age, BMI, involvement in co-design, baseline physical activity levels, baseline physical activity enjoyment, and baseline levels of the dependent variable will be identified using two-by-two tests and included in the model where appropriate.

The implementation of *Making a HIIT* will be evaluated using the Framework for Effective Implementation [20] across 8 components: 1) program reach – number of consenting schools and students; 2) dosage – number of HIIT workouts delivered and completed; 3) fidelity – students’ heart rate and RPE during HIIT workouts; 4) quality – variation in heart rate between students; 5) monitoring of control group – via heart rate; 6) responsiveness – student enjoyment and teacher perspectives; 7) adaption – modifications of the HIIT workouts by teachers; 8) differentiation – uniqueness of study.

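### The first HIIT questionnaire comes after co-design has finished, so analysing change from it misses any co-design effect already present, and the plan does not say which model term answers that objective

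*Protocol article*

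**What the plan says.** All references are to the Protocol article.

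- **Objective.** The second phase two objective begins: "Determine the effect of the co-design process on" and goes on to enjoyment, self-efficacy, affect, basic psychological needs and motivation towards HIIT.
- **When co-design happens.** Overview: "In phase one, students will co-design HIIT workouts with teachers and researchers". The two phases are described as "occurring during two subsequent terms in the same school year for each participating school".
- **Who receives it.** Phase one: "Only students in Group 1 will participate in this phase". It includes practical exposure to HIIT: "Students partake in several HIIT workouts, reflect on their heart rate".
- **When the scales are measured.** Under Pre-intervention and post-intervention measurements, the HIIT-specific questionnaires "will be collected after the first and last HIIT workout for all groups". The Intervention section places those two workouts in the 8-week phase two programme. No HIIT-specific scale is described before phase one.
- **Model.** The phase two Data analysis section assesses change in each scale with group (co-design or not), timepoint and their interaction.
- **Covariates.** Of the candidate covariates, the last listed and the rule for all of them read: "baseline levels of the dependent variable will be identified using two-by-two tests and included in the model where appropriate". The Enjoyment section adds: "Enjoyment of general physical activity will be used as a covariate for understanding enjoyment of HIIT specifically". General enjoyment (PACES) and the PAQ-C are both taken in the week before phase two.

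**The concern.** For an effect of co-design, a baseline has to precede co-design. Here Group 1 has finished the co-design lessons, and has tried and piloted HIIT workouts, before it first answers a HIIT questionnaire. Its first score already contains whatever co-design has done to enjoyment, autonomy or motivation by then.

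The model has the same form as the one for fitness. It suits fitness, which is measured in the week before and the week after the HIIT programme. It does not suit an exposure that ended before the first measurement. If the interaction is read as the co-design effect, a real and lasting benefit could be reported as no effect, and a benefit that partly wears off could be reported as harm. If the first score is entered as a covariate, part of the effect is adjusted away. General PACES and PAQ-C are also post-exposure for Group 1, though less directly tied to the outcome.

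**Working it through.** The plan gives no effect size, SD or sample size for these scales, so there is no figure of its own to reproduce on this point.

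**Notation.** Let δ₁ be the co-design effect on a scale at the first phase two workout and δ₂ the effect at the last, in SD units. Let b be the within-group slope of the last score on the first. With equal variances, b equals their correlation r.

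**What each estimate targets**, assuming no pre-existing group difference:

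- group × time: δ₂ − δ₁
- last score adjusted for the first: δ₂ − bδ₁, which is δ(1 − b) when δ₁ = δ₂ = δ
- group difference at the first workout: δ₁
- group difference averaged over both workouts: (δ₁ + δ₂)/2

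**Numbers put in** (0.5 and 0.25 SD, and b = 0.4, 0.6, 0.8, are assumptions):

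| Pattern | δ₁ | δ₂ | group × time | adjusted, b = 0.4 / 0.6 / 0.8 | first workout | average |
|---|---|---|---|---|---|---|
| Complete early, lasts | 0.5 | 0.5 | 0 | 0.30 / 0.20 / 0.10 | 0.5 | 0.5 |
| Grows | 0.25 | 0.5 | 0.25 | 0.40 / 0.35 / 0.30 | 0.25 | 0.375 |
| Fades | 0.5 | 0.25 | −0.25 | 0.05 / −0.05 / −0.15 | 0.5 | 0.375 |
| Arises only in the 8 weeks | 0 | 0.5 | 0.5 | 0.50 / 0.50 / 0.50 | 0 | 0.25 |

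**Simulation check.** 4,000 runs per pattern, 44 co-design students against 88 others (the 44 per group is borrowed from the shuttle run calculation), two-sided 5% test, no clustering, no pre-existing difference:

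- *Complete early, lasts:* group × time averages 0.00 SD and is significant in about 5% of runs, the false-positive rate. The adjusted estimate averages 0.30, 0.20 and 0.10 SD at r = 0.4, 0.6 and 0.8, with power 40%, 25% and 13%. The unadjusted last-workout difference averages 0.50 SD with power of about 76–77%.
- *Fades:* group × time averages about −0.25 SD, significant in 22%, 33% and 56% of runs as r rises. The adjusted estimate averages 0.05, −0.05 and −0.15 SD.
- *Arises only in the 8 weeks:* both estimates average about 0.50 SD, with power 69–99% (group × time) and 83–99% (adjusted). The same figures would apply if the first score had been taken before co-design.

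The averages agree with the formulas. The power figures are for comparison only, since clustering within classes would lower them.

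**The case against.** The strongest reply is that the Data analysis section does not single out the interaction. It lists group, timepoint and their product, and the descriptions of the individual scales speak of differences between groups as well as over time. The group term in that model is the difference at the first workout under reference coding, or the average over both under effect coding. This stands: the model can supply the right contrasts. What is missing is a statement that one of them is the co-design estimate, while the stated aim of the model is change.

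Second, adjustment for the first score is only a possibility. The covariate list serves both analyses and includes involvement in co-design, which is itself the exposure here, so not every item can be meant for this objective. This also stands, but nothing excludes the first score from the co-design model.

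Third, there is a practical reason for the timing: the Intervention section has the control group do two workouts so that its students can answer questions about HIIT. That explains the timing but does not make the score a pre-co-design baseline.

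Fourth, classes are not randomised and HPE staff help select them. A raw group difference may reflect class differences that predate co-design. This is a real limit on any remedy, and a reason not to simply drop PACES and PAQ-C.

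A reader might infer that the trial cannot answer this objective, or that the planned analysis removes the whole effect. The documents do not support that. The group term is in the model, adjustment is conditional, divergence over the 8 weeks is still captured, and complete loss needs a shift that is finished by the first workout and constant afterwards.

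**Conclusion.** The point holds in limited form. The first HIIT-specific score is post-exposure for Group 1, so change from it estimates only the further divergence over the programme. Whatever part of the co-design effect is present at the first workout cancels from group × time. The interaction is 0 for an effect that is complete by then and persists, and has the wrong sign as a co-design effect if that effect fades. Adjusting for the first score leaves δ(1 − b) of a persistent effect, or 0.4δ at the assumed b = 0.6. How much of a real effect falls before the first workout cannot be known from the documents.

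The defect is that the plan frames the analysis as change, does not name the group term as the answer to this objective, and leaves a post-exposure score among the candidate covariates. Fitness and executive function as effects of HIIT are not affected. This should be fixed, but it does not touch the main phase two outcome, which the sample size section gives as cardiorespiratory fitness.

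**What to change.** For the co-design objective, in the phase two Data analysis section:

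1. Name the effect as the co-design v no co-design difference at the first workout and averaged over the first and last workouts. Use Group 1 v Group 2 at both. Group 3 is also usable at the first workout, when it has done the same single phase two workout as Group 2. By the last workout it has not followed the HIIT programme, so including it there would mix co-design with HIIT.
2. Report group × time only as growth or fading of that difference. It is still needed, because an effect arising wholly within the 8 weeks is halved in the average (0.25 from 0.5 in the table).
3. Exclude the first-workout score from the covariates of this analysis.
4. Report results with and without general PACES and PAQ-C. They are measured after co-design, so adjusting may remove some effect, but they are also the main measured markers of prior class differences, so omitting them may leave confounding.
5. Where a school has not started, give these two existing questionnaires before phase one in all groups and adjust for those values.
6. State that, without randomisation or a HIIT measure before co-design, the group difference may include pre-existing class differences.

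Items 1 to 4 and 6 cost only wording and one extra set of model runs, and are possible where data collection has begun. Item 5 moves two short questionnaires to the earlier term; its downside is a longer gap before phase two.

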#### Anthropometry

Students will be asked to remove shoes, hats, and any heavy or bulky clothing. Stature will be measured using a stadiometer. Students will be asked to stand with their feet together and have their heels against the back of the stadiometer while keeping their knees straight. They will be instructed to breathe in and stand tall. Their stature will be recorded to the nearest 0.01 m. Body mass will be measured using a calibrated scale. Students will be asked to stand on the scale facing forward with their arms by their side. Their body weight will be recorded to the nearest 0.1 kg. Body mass index (BMI) will be calculated as (body mass (kg) divided by stature (m) squared). To determine students’ weight categories, age and sex specific BMI cut points will be used [30]. Based on discussions with key stakeholders (school gatekeepers and teachers), these measures will only be collected at the baseline visit and will be used as covariates in the study to understand differences based on body weight status.

#### General physical activity levels

Baseline general physical activity level data will be collected using the physical activity questionnaire for children (PAQ-C), a self-administered, 7-day recall instrument that generates a physical activity score based on eight items scored on a 5-point scale [31]. The questionnaire is reliable (ICC = 0.96) [32], and its convergent validity is supported through relationships with an activity rating question, a teacher’s rating of physical activity, and moderate to vigorous physical activity assessed by a separate inventory (*r* = 0.45 to *r* = 0.63) [33, 34]. Further, the PAQ-C is quick to complete (approximately 5 minutes), [35] and is one of three physical activity measures that received majority support within an expert group [34]. This questionnaire will only be completed prior to the intervention to understand participants baseline general physical activity levels, which will be used as a covariate in data analysis.

